### Hypotheses

After 6 months of home-based physical exercise, participants will show an improvement in cognitive (primary outcome) and physical functions measures (secondary outcomes), with larger gains in executive functions.Participants in the combined home-based physical exercise and cognitive training group will show greater improvements in cognition and physical functions post-intervention compared to participants who did not complete the cognitive training.

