## Methods/design

### Design

COVEPIC is a randomized, single-blind trial with two parallel intervention arms:
*Arm 1 – Physical exercise*: remote monitoring and counseling of home-based physical exercise.*Arm 2 – Physical exercise and cognitive training*: remote monitoring and counseling of home-based physical exercise and home-based cognitive training.

The study design includes six months of intervention. All participants will be assessed at baseline, 3 months, and 6 months. At each timepoint, four testing sessions will be done remotely using videoconference supervision and online questionnaires over a period of 7–10 days. At twelve months (6 months after the end of the intervention), a follow-up assessment will be performed to explore the potential maintenance of intervention effects. Participation in this follow-up assessment will be left to the participant's discretion, as it does not directly address the main hypotheses. The trial was designed according to SPIRIT guidelines (cf. SPIRIT checklist in the additional file) [28]. Figure 1 illustrates the trial design according to items of SPIRIT figure, which is also available in additional files.

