#### Primary outcome—Cognition

Cognitive functioning will be assessed via videoconference, using validated remote versions of paper-pencil neuropsychological assessments [37] and computerized tasks, both performed under the supervision of a research team member. G*eneral cognitive functioning* will be tested using a remote version of the Montreal Cognitive Assessment (MoCA) [38]. The remote version of the MoCA is identical to the original version, to the exception that one question in the orientation subscale is modified (“Now, tell me the name of this place, and which city it is in” was replaced by one question regarding an important sightseeing place in Canada). In addition, the *three main components of cognition* will be assessed with a comprehensive neuropsychological assessment, including both paper-pencil tests and computerized tasks, from which composite z scores will be calculated: executive functions, processing speed, and episodic memory. These different composite *Z*-scores will first be computed by grouping tests and subscores that conceptually assess the same cognitive functions (mean of *z*-scores of different tests and scores). In a second step, internal consistency among each composite *z*-score will be verified with Cronbach’s alphas as done previously (*α* > .7) [39]. The neuropsychological assessment will include the following paper-pencil tests that will be administered in a fixed order: Rey auditory verbal learning test [40], Digit Span, an oral Trail Making Test with three conditions (1—counting from 1 to 20 (maximum of 30s); 2—naming letters from A to Z (maximum of 30 s); 3—alternating between naming numbers and letters in chronological and alphabetical order (e.g., 1-A-2-B) (maximum of 30 s) [41]), Phonological and Semantic Fluency from the D-KEFS battery (Letters P, T, L (60 s maximum); Categories: animals, men’s names (60 s maximum); Switching between naming fruit and furniture (60 s maximum) [42]), and Similarities subtest from the WAIS-IV [43]. These tests are validated and normalized for an older adult population [40, 44, 45]. The Similarities subtest will only be administered at baseline to obtain a measure of crystallized intelligence; it will be optional and performed according to the level of the participant’s fatigue. Participants will also complete a computerized assessment on their tablet or computer [32]. The computerized tasks include a dual-task [32], Stroop task [33], and N-back [34], all in trained and transfer versions (same tasks but with different stimuli) presented in a counterbalanced order between the participants via a Latin square procedure. Subcomponents of each task allow the dissociation of attentional control mechanisms from mere cognitive speed. Importantly, the tasks record response time in milliseconds reducing the likelihood of ceiling effects. These tasks also tend to be more sensitive to training effects. The trained and transfer task comparison allows quantifying participants' ability to transfer cognitive training effects to another task. The computer equipment (i.e., computer or tablet) used by the participant for the computerized tasks will be systematically documented. Participants will be requested to use the same computer equipment for the four testing sessions.

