### Data analysis

#### Sample size calculation

The Montreal Health Innovations Coordinating Center**’**s biostatistics team completed the sample size calculation. The calculation was based on values available in the literature for physical exercise training alone [67], on different plausible values for the combined physical and cognitive training (since there are no values in the literature for this group), and on clinically relevant effect sizes to detect the cognitive outcome. A sample size of 49 subjects in each group will have 80% power to detect a difference in means of **−** 0.186 (the difference between a physical training alone mean of 0.239 and a combined training mean of 0.425, for an effect size of 0.624), assuming that the common standard deviation is 0.298 using a two-group *t* test with a 0.050 two-sided significance level. Considering a 20% attrition rate observed in our previous exercise studies, 61 participants will be recruited per intervention arm to ensure the targeted 49 participants per group (61 * .80 = 49) for a total of 122 participants.

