#### Planned data analysis

The variables in the study will be presented using descriptive statistics. The mean, standard deviation, median, minimum, Q1, Q3, and maximum will be presented for continuous variables. The number and percentage will be presented for nominal/ordinal variables. The statistical tests' assumptions will be examined, and data transformation or non-parametric analyses may be used as appropriate. SPSS and SAS version 9.4 or higher software will be used to conduct the analyses. Statistical tests will be two-tailed, and a *p* value of less than 0.05 will be considered as the indication of statistical significance.

Mean changes in cognitive performance from baseline will be analyzed using a repeated measures analysis of covariance (ANCOVA) model, adjusted for age, sex, education, and the dose of physical exercise, including the effects of the intervention (physical exercise alone or combined with cognitive training) and time (pre at baseline, mid at 3 months, post-intervention at 6 months). Observation of a statistically significant difference in the primary outcome between pre- and post-intervention timepoints will be considered as the evidence of the intervention's efficacy (i.e., primary hypothesis). The interaction between intervention arms (i.e., physical exercise alone or combined with cognitive training) and performance changes from pre to post-intervention will address the added value of the cognitive training compared to physical exercise alone (i.e., secondary hypothesis). Observation of a statistically significant *intervention × time* interaction in the primary outcome will be considered as the evidence that the differential effect operates by the exercises and combined interventions. Secondary and exploratory outcomes will be analyzed as the primary outcome.

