## Study limitation and development perspectives

Despite its strengths mentioned above, the proposed design presents some limitations. Due to this exceptional pandemic context, some ethical considerations refrained the research team from implementing a control group. Nevertheless, to address this limitation, at least partially, all participants will be included in the final analyses, without exclusion based on participation, to document the dose-response relationship between physical exercise and outcome effects. Additionally, sex was not taken into account in recruitment and randomization processes, although sex differences have been reported on cognition [74], as well as in exercise-training effects on cognition in healthy older adults [75]. Consequently, sex will be considered as a covariate in all statistical analyses. Also, a recent study from Peterman et al. [76] highlights that longitudinal changes in nonexercise prediction equations of cardiorespiratory fitness were associated with changes in cardiorespiratory fitness as measured by standardized VO2_max_ protocols but present significant errors in their predictions. Therefore, the use of nonexercise prediction equations could lead to a significant error in the estimated change of participants' cardiorespiratory fitness.

Future studies using more direct physical fitness assessments and tracking devices for remote monitoring could help better inform on the effect of physical exercise training in seniors. Indeed, adding a direct measure of physical fitness could help inform on participants' physical condition when they engage themselves in the intervention, as well as their progression. Its combination with a measurement of frequency, duration, and intensity of physical exercise sessions provided by tracking devices such as smartwatches or smart garments may shed light on the relationship between exercise training characteristics and the changes in physical fitness over the course of the intervention. This kind of information may substantially improve remote monitoring, helping the training coaches provide resources and recommendations adapted to each participant according to their physical fitness and progression.

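### A baseline-to-6-month change is taken as evidence of efficacy although both arms exercise and there is no untreated control, so practice and calendar effects cannot be separated from it

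*Protocol article*

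**What the plan says.** All references are to the protocol article.

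- **Hypotheses.** The first hypothesis is a within-participant improvement: "After 6 months of home-based physical exercise, participants will show an improvement in cognitive (primary outcome" and so on. The second is that the combined arm improves more.
- **Planned data analysis.** A repeated measures ANCOVA contains arm and time (baseline, 3 and 6 months). A "statistically significant difference in the primary outcome between pre- and post-intervention timepoints will be considered as the evidence of the" intervention's efficacy; this is named the primary hypothesis. The interaction of arm with change "will address the added value of the cognitive training compared to physical exercise alone (i.e., secondary hypothesis").
- **Design and Interventions.** Arm 1 is remotely monitored exercise. Arm 2 is the same exercise plus cognitive training. "All participants will be assessed at baseline, 3 months, and 6 months".
- **Sample size calculation.** The 49 per group are for a two-group t test on "the difference between a physical training alone mean of 0.239 and a combined training mean of 0.425".
- **Study limitation and development perspectives.** The article states that "some ethical considerations refrained the research team from implementing a control group". It continues: "Nevertheless, to address this limitation, at least partially, all participants will be included in the final analyses, without exclusion based on participation", so that dose-response can be studied.

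**The concern.** The efficacy rule is a comparison over time with nothing to compare it against. Anything that moves cognitive scores between baseline and 6 months in both arms feeds into it. The article itself points to two such sources.

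- **Practice.** Table 1 lists the MoCA, the oral Trail Making Test, fluency, digit span, the Rey list and the computerised tasks at every assessment. Of the computerised tasks the article says "These tasks also tend to be more sensitive to training effects", and the combined arm also practises dual-task, Stroop and N-back at home.
- **Calendar change.** Recruitment runs from May 2020 to August 2021, and the Physical exercise section expects confinement rules to change during the study. This could raise or lower scores.

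At stake is the main conclusion. An upward drift would be reported as efficacy when exercise had done nothing, and a downward drift could hide a real benefit. Meanwhile the comparison that randomisation protects, and that the sample size serves, is placed second.

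**Working it through.** **1. The plan's own calculation, to see which hypothesis it serves.** Inputs (Sample size calculation): means 0.239 and 0.425, SD 0.298, two-sided 0.05, 49 per group.

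- Difference: 0.425 − 0.239 = 0.186. Effect size: 0.186 / 0.298 = 0.624, as stated.
- The exact two-group t test needs 42 per group for 80% power. With 49 per group, the noncentrality is 0.624 × √(49/2) = 3.09 and power is 86.4%.
- The stated 49 is thus not reproduced, but the discrepancy is on the safe side and does not affect this point.
- The calculation concerns the difference between arms, that is, the secondary hypothesis. The article gives none for the pre-post change that it calls primary.

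**2. The pre-post rule when treatment does nothing.** Simplification: a one-sample t test on change from baseline to 6 months, both arms together, n = 2 × 49 = 98, true treatment effect zero, common drift m.

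- Noncentrality = m√n / SD of change; critical value t(0.975, 97) ≈ 1.985.
- The article calls 0.298 a common standard deviation and does not say that it is the SD of change. I take it as one case and assume 0.6 and 1.0 as others. The drift values are also assumptions.
- At SD 0.298, the smallest significant mean change is 1.985 × 0.298 / √98 = 0.060.
- For m = 0.10, the noncentrality is 0.10 × 9.90 / 0.298 = 3.32, and likewise 1.65 at SD 0.6 and 0.99 at SD 1.0.

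Probability that the rule declares efficacy (n = 98):

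| Common drift | SD of change 0.298 | 0.6 | 1.0 |
|---|---|---|---|
| 0 | 5% | 5% | 5% |
| 0.05 | 38% | 13% | 8% |
| 0.10 | 91% | 37% | 17% |
| 0.15 | 99.9% | 69% | 31% |

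For a drift of 0.10, the figures are 95.7%, 44.7% and 19.5% if all 122 are analysed. In a single arm of 49 they are 63.4%, 20.8% and 10.5%.

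**3. The randomised contrast under the same drift.** In 20,000 simulated trials with 49 per arm, SD 0.298 and no arm difference:

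| Common drift | Pre-post rule significant | Between-arm test significant |
|---|---|---|
| 0 | 5.2% | 4.8% |
| 0.10 | 91.0% | 4.9% |
| 0.239 | 100% | 5.1% |

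Drift shared by both arms cancels in the between-arm difference. It does not cancel in the time effect.

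**4. Does the dose-response analysis supply a comparator?** No. The Interventions section lets participants adjust their dose as they wish, and the dose terciles are formed from what they chose to do. Dose groups are self-selected, not randomised. Adjusting the main model for dose does not create an unexposed group either.

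**The case against.** The strongest reply is that the article is open about the limitation. It gives an ethical reason for having no control group, offers dose-response only as a partial remedy, and keeps the randomised contrast with its own hypothesis, decision rule and sample size. That stands as a defence of the design: the absence of an untreated arm is not the fault, and nothing is concealed. It does not rescue the efficacy sentence, which the disclosure leaves unchanged.

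Several stronger readings are tempting but not supported:

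- **That the trial will almost certainly declare efficacy.** The documents give no practice or secular-trend figure, and the probability depends heavily on the SD of change, as the table shows.
- **That the pandemic would push scores up as lockdown eased.** The article's own background expects isolation and inactivity to harm cognition. With staggered recruitment, six-month windows may include tightening as well as easing. Practice is the only clearly upward source.
- **That regression to the mean would produce false gains.** The entry screen is a minimum score on a telephone MMSE, which excludes low scorers and is not an outcome. Nothing here supports that mechanism.
- **That a significant decline would count as success.** The rule is worded as a two-tailed difference, but the first hypothesis specifies improvement. This is a minor matter of wording.
- **That the pre-post contrast is certainly pooled over arms, or the test forms certainly identical.** The article does not settle either, and a full protocol may. Estimating the contrast within the exercise arm would not supply a comparator, and alternate forms would leave the calendar problem.

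**Conclusion.** The point holds. The efficacy rule for the primary hypothesis draws a causal conclusion that a design with exercise in both arms and no untreated control cannot support. The article's only randomised comparison, for which the sample size was computed, is ranked below it.

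The size is conditional. With 98 completers, zero treatment effect and an assumed common drift of 0.10, the chance of a false efficacy statement ranges from about 17% to about 91% over the SDs considered, against about 5% for the between-arm test. The calculation uses a simple t test on change in place of the repeated measures ANCOVA. The conclusion that the inference is unsupported does not depend on these figures; only its likely frequency does.

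**What to change.** 1. Replace the efficacy sentence in Planned data analysis. Report a pre-post difference only as change over time: within-arm means with 95% confidence intervals, the exercise-alone arm shown separately, and an explicit caveat on practice and calendar time.
2. Base any efficacy statement on the randomised between-arm difference in change from baseline to 6 months, and limit it to the added value of cognitive training. Show the trained versions of the computerised tasks apart in that contrast, because only the combined arm practises them at home; that familiarity is not shared drift and does not cancel.

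**Cost.** No new data or participants: on the article's own inputs, 49 per arm give 86.4% power for this contrast. The trial gives up a causal claim about exercise alone. It is more than a wording change: under Ethical considerations, a significant change of objectives needs a formal amendment, ethics board approval before implementation and an update to the published record. It would also come late, with recruitment due to end in August 2021, so the amendment should be dated and its reason stated.

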
**Table 1 Tab1:** List of assessments across the study timepoints according to the remote method used

Remote method	Domain	Procedure	T-1	T0	T1	T2	T3
**Phone call**	**-**	Written informed consent	X				
		Mini-Mental State Examination	X				
		Physical activity readiness questionnaire	X				
		Technology tutorial	X				
**Online videoconference**	**Cognition**	Montreal Cognitive Assessment		X	X	X	X
		Oral Trail Making Test		X	X	X	X
		Verbal Fluency Test		X	X	X	X
		Digit Span test		X	X	X	X
		Similarity Test		X	X	X	X
		Rey auditory verbal learning test		X	X	X	X
		Computerized trained cognitive task		X	X	X	X
		Computerized transfer cognitive task		X	X	X	X
	**Physical functions**	One leg balance test		X	X	X	X
		5-time Sit-to-stand test		X	X	X	X
		Timed Up and Go test		X	X	X	X
		4-meter walking speed test		X	X	X	X
**Online self-reported forms**		Matthews Questionnaire		X	X	X	X
	**Quality of life**	12-Item Short Form Survey		X	X	X	X
	**Mood and anxiety**	State Anxiety Inventory		X	X	X	X
		Geriatric Depression Scale		X	X	X	X
		Perceived Stress Scale		X	X	X	X
		Perseverative Thinking Questionnaire		X	X	X	X
		Connor-Davidson Resilience Scale 10		X	X	X	X
		Intolerance of Uncertainty Scale		X			
		Trait Anxiety Inventory		X			
		Anxiety sensitivity Index		X			
	**Social environment**	Social and Community Involvement Questionnaire		X	X	X	X
		Lubben Social Network Scale		X	X	X	X
	**Sleep**	Pittsburgh Sleep Quality Index		X	X	X	X
		Berlin Questionnaire		X	X	X	X
	**Nutrition**	Short Diet Questionnaire		X			X
	**Prior Physical activity**	Physical Activity Scale for the Elderly		X			
	**Cognitive reserve**	Cognitive reserve Questionnaire		X			
	**Gender**	Bem Sex-Role Inventory		X			
	**Medical history**	Medical Questionnaire		X			
	**COVID-19 repercussions**	QCOVID Questionnaire		X			

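### A significant pre-post change is declared evidence of efficacy, but with two active arms and a repeated test battery it cannot be separated from retest gain or other time effects

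*Protocol article*

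**What the plan says.** The Hypotheses section expects that, after six months of home-based exercise, "participants will show an improvement in cognitive (primary outcome" and physical measures. Planned data analysis turns this into a decision rule: "statistically significant difference in the primary outcome between pre- and post-intervention timepoints will be considered as the evidence". What is thereby declared is that the programme works, and the article labels this its primary hypothesis. The comparison between the randomised arms comes second. The arm-by-change interaction "will address the added value of the cognitive training compared to physical exercise alone (i.e., secondary hypothesis".

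The Design section describes two parallel arms, exercise alone and exercise plus cognitive training, so every participant receives an active programme. It also states: "All participants will be assessed at baseline, 3 months, and 6 months". Table 1 marks the MoCA, oral Trail Making, verbal fluency, Digit Span, the "Rey auditory verbal learning test" and the computerised trained and transfer tasks at each of these visits.

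The limitations section says that "some ethical considerations refrained the research team from implementing a control group". As a partial answer it keeps all participants in the analysis and explores dose-response. The efficacy rule is left as it stands.

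**The concern.** The rule compares mean change with zero. Zero is the right no-effect value only if scores would have stayed level without the programme. When a battery is repeated over six months, familiarity with the tests is a plausible source of gain. Anything else that moves with calendar time, including changing pandemic conditions, also enters the same mean change. With no untreated group, nothing in the design shows what change would have occurred anyway.

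What is at stake is the trial's primary conclusion. Following the plan as written, the investigators could report that the intervention is efficacious for cognition when it has no effect, and the stated 5% error rate would not describe how often that happens.

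**Working it through.** **1. The plan's own figure.** Sample size calculation gives means of 0.239 and 0.425, a common SD of 0.298, two-sided alpha 0.05, 80% power and 49 per group.
- Effect size: (0.425 − 0.239)/0.298 = 0.186/0.298 = 0.624, as stated.
- Exact two-sample t test: 80% power needs 41.3, so 42 per group (power 80.7%). With 49 per group, power is 86.4%.

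The stated 49 is therefore not reproduced at 80% power. The discrepancy is conservative and does not bear on this point. What matters here is that the calculation sizes the comparison between the arms, not the pre-post test named as primary.

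**2. Inputs for the pre-post rule.**
- Completers: 49 + 49 = 98 (Sample size calculation).
- SD of change: 0.298, 0.5 or 1.0. The plan does not say whether its 0.298 is an SD of change or of level, so all three are assumptions.
- Retest or time gain common to both arms: 0.05, 0.10 or 0.15 z. The documents give no value, so these are assumptions.
- Intervention effect: zero.

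**3. Smallest significant mean change.** This is t(0.975; 97) × SD/√98, with t = 1.985.
- SD 0.298: 1.985 × 0.298/9.899 = 0.060
- SD 0.5: 1.985 × 0.5/9.899 = 0.100
- SD 1.0: 1.985 × 1.0/9.899 = 0.200

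**4. Chance of a significant result with no intervention effect.** The one-sample t statistic follows a noncentral t distribution with 97 degrees of freedom and noncentrality gain × √98/SD. For example, a gain of 0.10 at SD 0.298 gives 0.10 × 9.899/0.298 = 3.32 and a rejection probability of 91%.

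| Common gain (z) | SD 0.298 | SD 0.5 | SD 1.0 |
|---|---|---|---|
| 0 | 5% | 5% | 5% |
| 0.05 | 38% | 17% | 8% |
| 0.10 | 91% | 50% | 17% |
| 0.15 | 99.9% | 84% | 31% |

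**5. The randomised contrast under the same conditions.** Both tests were simulated 20,000 times with 49 per arm, SD 0.298, equal gain in both arms and no treatment effect.

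| Common gain (z) | Pre-post rule | Between-arm test |
|---|---|---|
| 0 | 5.2% | 4.8% |
| 0.1 | 91% | 4.9% |
| 0.2 | 100% | 5.1% |

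A gain shared by both arms cancels in the between-arm test and does not cancel in the pre-post rule.

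**6. Whether dose-response fills the gap.** The Interventions section lets participants adjust their own dose. Comparing dose groups is therefore observational. All dose groups also sit the same repeated tests, so the comparison does not show what change would occur with no programme.

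**The case against.** The strongest defence is that the article is open about its design. It discloses the missing control group and gives an ethical reason. It prespecifies the randomised interaction and sizes the trial for it. It also includes transfer tasks with different stimuli. All of this is true, and the absence of a control arm is not the fault raised here. But the disclosure leaves the efficacy wording untouched, and the transfer tasks are themselves repeated at every visit.

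The figures are also open to challenge. They come from an unadjusted t test, not the planned repeated-measures ANCOVA. They do not apply to the MoCA, which is not a z-score. They also fall sharply as the SD rises. This stands: they are illustrations, not estimates of this trial's error rate.

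Three stronger readings are tempting, and the documents do not support them.
- A reader might infer that a significant decline would count as efficacy, since the rule speaks of a two-tailed difference. The rule is tied to the primary hypothesis, which is stated as an improvement, and two-tailed testing of a directional hypothesis is ordinary practice.
- A reader might take "paper-pencil tests that will be administered in a fixed order" to mean that identical forms are reused. The phrase concerns the order of tests within the battery. The article does not say whether alternate word lists or MoCA forms are used, and an article may leave that to the full protocol.
- A reader might conclude that practice gains are certain here. No part of the article says so. They are a plausible explanation that the design cannot exclude.

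**Conclusion.** The concern holds for the efficacy wording under Planned data analysis. With two active arms and a battery repeated at 0, 3 and 6 months, a significant pre-post change shows that scores moved, not that the intervention moved them. This follows from the stated rule and design and does not depend on any assumed number.

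The size does depend on assumptions. Across common gains of 0.05 to 0.15 z and change SDs of 0.298 to 1.0, the chance of an efficacy claim with no effect runs from 8% to 99.9%. It exceeds the nominal 5% in every case examined. Because the rule governs the primary conclusion, it should be changed before analysis.

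**What to change.** In Planned data analysis, remove the statement that a significant pre-post difference is evidence of efficacy. Report the pre-post change with its 95% CI as change under the programme, including retest and time effects. Limit efficacy conclusions to the randomised intervention × time contrast, read as the added value of cognitive training over exercise alone. That test is already planned, and at the plan's own inputs 49 per arm gives it 86.4% power, so no participants, visits or arms need to be added.

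One caution on reading that contrast: the combined arm trains on the dual-task, Stroop and N-back tasks, and their trained versions are also in the outcome battery. A between-arm difference on those scores can reflect task-specific practice.

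The cost is a change of wording and a narrower claim. The trial would no longer assert the efficacy of exercise alone from pre-post change.
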